#### Subgroup analyses

Subgroup analyses will be performed for the primary outcomes. The subgroups are defined as follows:Patient-level characteristics:Age (< 5, 5–11, and 11+)Sex (boys vs. girls)Ethnic groupAsthma diagnosis (< 5, 5+)Read receipt vs not read (email that sent to GPs)GP IMD quintile

Each subgroup analysis will be carried out by adding the subgroup variable into the main logistic regression model. Summary measures for each group will comprise prescription uptake counts and percentages within each arm, as well as the OR for effect with a 95% CI.

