### The intervention

Selected GP practices currently registered with CPRD and randomised to the intervention arm will receive correspondence twice, once by email and once by mail. The intervention is a letter that highlights the drop in prescription uptake for children with asthma during the summer holidays and introduces the results of the PLEASANT trial. In addition, it advises GP practices on the effect of reminding parents of children with asthma to continue taking their asthma preventer medications during the summer holidays. It will be sent with the assistance of the CPRD to the CPRD contact lead at GPs along with the named to the practice manager and asthma lead. The plan, subject to confirmation and amendment, is that the intervention will be sent by July 2021, which is the advice from the trial steering committee (TSC). Given the timing of the intervention, the hope is that GP practices will then send their correspondence to parents during the school holidays. It is hoped the intervention can be timed to enable sufficient time for GP practices to implement the advice from the intervention.

As this is an implementation study, the correspondence to GP practices is advisory, and the decision on implementation is down to the individual GP practices.

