### Randomisation and allocation concealment

Practices will be allocated 1:1 to intervention or control to ensure an equivalent sample size in each arm of the study in terms of the number of children with asthma. The randomisation will be stratified by the size of the practice as assessed by decile within the CPRD. All the practices in the study will be known from the CPRD and will not be prospectively recruited. GP practices randomised to the intervention will receive a postal bulletin and an email advising them to implement the study. GP practices randomised to control will not receive postal bulletin or email, and they will continue with usual care.

For practices included in the study, randomisation will be undertaken by study statistician using bespoke Excel spreadsheet. A file with anonymous practice identification codes and the stratification number will be provided to the CPRD. The statistician will not receive any information that would identify the practices.

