#### Data analysis

Statistical methods appropriate to a cluster randomised trial will be used for the analysis of the data. The statistical analysis will be performed on an intention-to-treat-basis and reported according to CONSORT guidelines for Cluster RCTs [17]. A dropout of practices is not expected. Some practices may merge, close, or split. Small numbers are likely to be involved, but no special treatment is necessary and no imputation is planned.

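### Email read receipt is planned as a treatment-effect subgroup, but it arises after randomisation and only in the intervention arm, so no randomised subgroup odds ratio can be formed from it

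*Protocol article*

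**What the plan says.** Under Subgroup analyses, the protocol article includes "Read receipt vs not read (email that sent to GPs") in the list of subgroups for the primary outcome. One method covers every item on the list: "Each subgroup analysis will be carried out by adding the subgroup variable into the main logistic regression model". The promised output for each group is "prescription uptake counts and percentages within each arm, as well as the OR for effect with a 95% CI".

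Two other sections fix who can have a read status. Under The intervention, practices "randomised to the intervention arm will receive correspondence twice, once by email and once by mail". Under Randomisation and allocation concealment, "GP practices randomised to control will not receive postal bulletin or email, and they will continue with usual care".

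The Data analysis section sets the general principle: "The statistical analysis will be performed on an intention-to-treat-basis".

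**The concern.** A subgroup analysis of a treatment effect needs a variable that is defined in both arms and cannot be influenced by allocation. Read receipt is neither. It comes into being only once the email has been sent, and none of the 695 control practices can have one. The output promised for each subgroup therefore has no control column for readers.

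Any odds ratio that is produced will rest on practices sorting themselves into readers and non-readers. The Discussion says that practices will not be contacted to check what they did, so the receipt is the only marker of engagement that the article names. A reader could easily take an odds ratio for readers as the effect of the letter once read, when part or all of it may be selection.

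**Working it through.** **Inputs from the article (Sample size):** 694 intervention and 695 control practices, 85 children per practice, 30% uptake, intraclass correlation 0.03, stated 95% half-width 1%.

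**Assumptions, not in the article:** the share *f* of intervention practices that read the email, the gap *d* in underlying uptake between readers and non-readers, and a true effect of zero.

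**1. The plan's own figure.**
- Design effect = 1 + (85 − 1) × 0.03 = 3.52.
- Children: 694 × 85 = 58,990 and 695 × 85 = 59,075.
- Half-width for the difference between arms = 1.96 × √[0.30 × 0.70 × 3.52 × (1/58,990 + 1/59,075)] = 0.98 points.

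This agrees with the stated 1%. The sample-size statement is not in question here.

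**2. What the planned model can estimate.** There are four ways to run it.
- *Control read status left missing:* controls drop out, arm is constant, and no arm effect remains.
- *Controls coded as not read, with an arm-by-read term:* arm × read equals read in every practice. The design matrix has 4 columns (intercept, arm, read, arm × read) but rank 3, so the interaction cannot be estimated.
- *Controls coded as not read, main effects only (closest to the wording):* the model can be fitted. The arm odds ratio then compares non-readers with all controls, and the read odds ratio compares readers with non-readers inside the intervention arm. Neither comparison was randomised.
- *Readers and non-readers each set against all controls:* this can be estimated, but each intervention subset is self-selected.

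**3. Illustration of size (unadjusted).** With no true effect, readers minus controls = (1 − *f*)*d* and non-readers minus controls = −*fd*. The two cancel over the whole arm: *f*(1 − *f*)*d* − (1 − *f*)*fd* = 0.

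For *f* = 0.4:
- Half-width, readers v controls = 1.96 × √[0.21 × 3.52 × (1/(0.4 × 58,990) + 1/59,075)] = 1.30 points.
- Half-width, non-readers v controls (0.6 in place of 0.4) = 1.13 points.
- *d* = 2 points: readers +1.2, non-readers −0.8. Both lie inside their half-widths.
- *d* = 5 points: readers +3.0, non-readers −2.0. Both lie outside.
- Gap at which the reader effect equals its half-width = 1.30 / 0.6 = 2.2 points.

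The same calculation over a range of read shares:

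| Assumed read share | Half-width, readers v controls | Gap that reaches it | Half-width, non-readers v controls | Gap that reaches it |
|---|---|---|---|---|
| 20% | 1.70 | 2.1 | 1.04 | 5.2 |
| 40% | 1.30 | 2.2 | 1.13 | 2.8 |
| 50% | 1.20 | 2.4 | 1.20 | 2.4 |
| 80% | 1.04 | 5.2 | 1.70 | 2.1 |

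(All in percentage points.) For scale, the article's 30% rate and intraclass correlation of 0.03 imply a between-practice standard deviation of √(0.03 × 0.21) = 7.9 points, so a gap of 2.2 points is about 0.28 of a standard deviation.

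**4. Meaning of an unread email.** Each intervention practice is contacted by post as well as by email. A practice without a receipt may still have read the posted letter, so the read/not-read split does not separate exposed from unexposed practices either.

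**The case against.** The strongest reply is that this is one item in a list of subgroups, and that an analysis plan not shown here may say how controls are coded or may recast the item as a descriptive or compliance analysis. The article does not describe it in that way. It gives the item the same treatment-effect output as the baseline subgroups, and no coding of controls turns that output into a randomised comparison. A complier-average analysis would keep the randomisation, but it must assume that the letter acts only through the read email, which the posted copy makes doubtful.

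Other parts of the reply do stand:
- **The model is not wholly inestimable.** A reader might infer that it cannot be fitted at all. The article states no interaction term, and with controls coded as not read the main-effects model runs. What cannot be estimated is the odds ratio among readers and the interaction.
- **A false positive is not guaranteed.** A reader might infer one from the illustration. The read share and the gap are assumptions, and the smaller gaps stay inside the half-widths. The figures also ignore the main model's adjustment for baseline preventer prescriptions, which may absorb part of any stable difference between practices.
- **The direction of selection is unknown.** It is tempting to suppose that readers are the better-organised practices, but nothing in the article says so.
- **The heading over the list proves nothing.** The item follows "The subgroups are defined as follows:Patient-level characteristics" although a receipt belongs to a practice. The practice-level deprivation quintile sits in the same run of text, so this may be formatting, and it has no analytic consequence.

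**Conclusion.** The point holds as a defect in one planned subgroup analysis. It follows from three sections of the article read together and needs no outside figure: read status arises after allocation, exists in one arm only, and cannot support the odds ratio that is promised.

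The size of any distortion cannot be known from the article. Under the stated assumptions (no true effect, 40% reading, no covariate adjustment), it exceeds the 1.3-point half-width for readers once the gap passes about 2.2 points. Over read shares of 20% to 80%, that threshold runs from 2.1 to 5.2 points.

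A reader might infer that the trial's main result is compromised. It is not: the primary analysis compares the arms as randomised and does not use read status. The item should be corrected, but it is not a condition for the validity of the trial.

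**What to change.** In Subgroup analyses, and wherever the analysis plan repeats the list, remove read receipt from the subgroups for which a treatment effect is reported. Report it instead as a process measure: the percentage of intervention practices with a receipt. If its association with uptake is shown, confine it to the intervention arm, label it non-randomised, give no treatment odds ratio, and note that the same practices were also contacted by post.

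The cost is a change of wording and the loss of the planned subgroup odds ratio. No data collection, sample size or primary analysis changes. Trial status describes the data as still being cleaned before analysis, so at that stage the change could be made before any results were seen.

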### Statistics

#### Sample size

The sample size is based on feasibility and the anticipated number of practices providing data to the CPRD. We anticipate a sample size of approximately 1389 GP practices (694 on intervention and 695 on control). Alongside this, from the previous study (PLEASANT), we also anticipate 85 school-age children having asthma per practice [14]. Assuming an expected rate of 30% of people collecting their prescription and an intraclass correlation of 0.03, it is anticipated that the precision of the estimates in the study—estimated as a half-width of a 95% confidence interval—will be 1%.

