#### Primary analysis

The proportion of children having a preventer prescription collected within the primary time period per child will be analysed using a random effect logistic regression model with the individual’s age, sex, number of preventer prescriptions in the baseline period as covariates, the trial arm (intervention or control) as a fixed effect, and the design/cluster effect of general practice as a random effect. Effect sizes (assessed as an odds-ratio) and 95% confidence intervals for the primary endpoint will be presented. The number of prescriptions per child will be similarly analysed separately for each time period using negative binomial regression.

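### The subgroup model as described has a single arm term and no arm-by-subgroup interaction, so it cannot give the per-group odds ratios the same section promises, or test whether they differ

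*Protocol article*

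**What the plan says.** The Subgroup analyses section lists age band, sex, ethnic group, asthma diagnosis, email read receipt and practice IMD quintile. It then gives one rule for all of them: "Each subgroup analysis will be carried out by adding the subgroup variable into the main logistic regression model". The next sentence sets the output: "Summary measures for each group will comprise prescription uptake counts and percentages within each arm, as well as the OR for effect with a 95%" confidence interval.

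The main model is defined under Primary analysis as a "random effect logistic regression model with the individual’s age, sex, number of preventer prescriptions in the baseline period as covariates", with "the trial arm (intervention or control) as a fixed effect, and the design/cluster effect of general practice as a random effect".

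No interaction term, heterogeneity test or ratio of ORs is mentioned anywhere in the article. The Discussion counts it as a strength that the sample allows several subgroup analyses with enough power, but gives no figure.

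**The concern.** A subgroup analysis asks whether the effect of informing practices differs between kinds of children or practices. Entering a variable alongside a single arm term answers another question: whether that variable predicts prescription uptake. The treatment effect stays one number, shared by all groups.

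The two consecutive sentences in the section therefore do not fit together. The first describes a model with one treatment OR; the second promises one per group. An analyst following the text would have to depart from it, either by adding an interaction or by fitting each group separately. Separate fits describe each group but do not test a difference between them. The choice matters because a statement that the letter worked better in one group needs a test of that difference, and the method as described supplies none.

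**Working it through.** **1. The plan's own figure.** Inputs from Sample size: "approximately 1389 GP practices (694 on intervention and 695 on control"), 85 children per practice, 30% uptake, intraclass correlation 0.03.
- Design effect = 1 + (85 − 1) × 0.03 = 3.52.
- Half-width = 1.96 × √[0.3 × 0.7 × 3.52 × (1/(694 × 85) + 1/(695 × 85))] = 0.98 percentage points.

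This matches the stated 1%. It concerns the overall comparison, and nothing below changes it.

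**2. What the described model yields.** For child i in practice j with subgroup indicator S:
- As described: logit(p) = β0 + β1·arm + (age, sex, baseline prescriptions) + γ·S + practice effect. The arm OR is exp(β1) whether S = 0 or S = 1.
- With an interaction, δ·arm·S is added. The arm OR is exp(β1) when S = 0 and exp(β1 + δ) when S = 1. The ratio of ORs is exp(δ), and the test of δ = 0 is the test of effect modification.

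**3. Sex and age.** Sex is already in the model, so adding it changes nothing and the result is the primary analysis again. Age is also there, but its form (continuous or banded) is not stated, so adding the bands could alter the fit slightly. There would still be one arm OR.

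**4. Illustration.** Assumed, not from the protocol: two equal groups and true ORs of 1.30 and 1/1.30 = 0.77. The control rate of 30% is the protocol's. Expected counts were fitted by ordinary logistic regression without the practice random effect; the structural result does not depend on it, because arm still enters once.
- Control odds = 0.30/0.70 = 0.4286.
- Group A intervention: odds 0.4286 × 1.30 = 0.557, rate 35.8%.
- Group B intervention: odds 0.4286/1.30 = 0.330, rate 24.8%.
- Mean intervention rate 30.3%.

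| Model | OR, group A | OR, group B |
|---|---|---|
| Arm only | 1.014 | 1.014 |
| Arm + subgroup (as described) | 1.014 | 1.014 |
| Arm + subgroup + interaction | 1.30 | 0.77 |

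The ratio of ORs in the last model is 0.77/1.30 = 0.59.

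**5. Precision of the interactions.** The protocol gives none. These are approximations on the risk-difference scale, using 694 practices per arm.
- Sex, assuming a 50/50 split within practices and a shared practice effect that cancels: SE = √[4 × 0.21 × 0.97/(694 × 42.5)] = 0.53 points. Half-width = 1.0 point; difference detectable with 80% power = 2.80 × 0.53 = about 1.5 points.
- Top against bottom IMD quintile, assuming equal fifths of practices (138.8 per arm): SE = √[4 × 0.21 × 3.52/(138.8 × 85)] = 1.58 points. Half-width = 3.1 points; detectable difference = about 4.4 points.

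Interaction precision thus varies widely across the listed subgroups, so one general statement of adequate power tells the reader little.

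**6. Read receipt.** One listed subgroup is "Read receipt vs not read (email that sent to GPs"), but "GP practices randomised to control will not receive postal bulletin or email". Read status has no control-arm counterpart. If controls were coded as unread, the product of arm and read status would equal read status itself, so no interaction is estimable. Read status also arises after randomisation.

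**7. Age bands.** The bands are under 5, 5–11 and 11+. A child aged 11 fits the last two labels. Eligible ages run from 4 to 16, which is 13 ages, so the assignment of one of the 13 is undefined.

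**The case against.** The strongest reply is that an interaction was intended. The output sentence promises an OR for each group, and adding sex to a model that already holds it would be pointless, so the first sentence may be loose wording for an arm-by-subgroup term. The article is also condensed, and its analysis plan, which is not shown, may specify the interaction. It is right that intent cannot be read off the page. But the article does not merely leave the method open: it names one, and that method does not deliver the output in the next sentence.

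A second reply is that the illustration builds in the heterogeneity it then shows being averaged away. That is correct. It shows how the model behaves and is not an estimate of error in this trial.

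Several stronger readings are tempting but unsupported:
- A reader might infer that the investigators plan to compare p-values across subgroups, or will claim the letter works better in some group. The section mentions only counts, percentages, ORs and intervals, and makes no such claim.
- A reader might infer that 11-year-olds would be counted twice. A child takes one level of a categorical variable, so only an ambiguous label is established.
- A reader might infer that one interaction rule would mend every listed subgroup. Read receipt shows that it would not.
- A reader might infer damage to the main result. The primary model does not depend on the subgroup section.

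**Conclusion.** The point holds as a fault in a stated rule. Read literally, the subgroup method gives one common OR, repeats the primary model for sex, cannot supply the group-specific ORs promised in the following sentence, and contains no test of effect modification. This follows from the form of the model and needs no numerical assumption. The illustrative figures (1.014 against 1.30 and 0.77) rest on the assumed effects, and the interaction precisions rest on the assumed subgroup splits.

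The conclusion is limited to the five subgroups defined in both arms; read receipt is a separate problem. The age-band overlap is a minor labelling slip. The matter should be fixed, but it does not threaten the trial's main conclusion: the primary estimate and the 1% precision stand.

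**What to change.** Replace the single rule with text along these lines:

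- For age, sex, ethnic group, asthma diagnosis and practice IMD quintile, fit the primary random-effect logistic model with the subgroup variable and its interaction with trial arm. Report the interaction test and the ratio or ratios of ORs with 95% confidence intervals, and derive the subgroup-specific ORs and intervals from that same model.
- Take read receipt out of this rule. Label it a separate exploratory analysis of a post-randomisation variable observed only in the intervention arm.
- Make the age bands mutually exclusive, for example under 5, 5 to 10 and 11 to 16.

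If the analysis plan already specifies the interaction, it is enough to state that and align the two documents. The cost is a few sentences and no new data. Trial status reports that the data were being cleaned and analysis had not begun; if that is still so, the change can be recorded before any result is seen.

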#### Information governance

TRAINS (TSC) was established to oversee the study from an independent perspective. The TSC consist of two academic GP, practice nurse, practice manager, and statistician. The role of the TSC is to provide advice on the study, ensure the delivery of the intervention, and achieve the project outcomes. Also, it focused on the intervention design. The TRAINS Trial Steering Committee provides guidance, support, and input to the development of the trial.

#### Patient and public involvement in the design of the trial

During the design of the TRAINS trial, two seminar meetings were arranged with the Academic Unit of Primary Care. The first was held in January 2020, and the second seminar was planned for March 2021, involving 16 GPs plus researchers and teaching staff. These events were used to investigate the designing of the intervention, to get feedback on to whom the letter should be addressed (i.e. addressed to practice manager, asthma lead, or both), to discuss the timing of sending the intervention (i.e. June and July). The first initial PPI event was written up and uploaded onto the figshare website [18]*.*

## Discussion

TRAINS is a large pragmatic cluster randomised controlled trial that will assess the effectiveness of a brief postal intervention sent to GP practices informing them about the PLEASANT trial results, evidenced by an increase in prescription uptake during the summer holiday. The advantage of the study design is that it has an efficient study design using the CPRD to get the data. The GP practices will not know if they are in the study and will not be recruited into the trial for data collection. GP practices are free to implement the learnings from PLEASANT as they see fit.

The strengths of the study that as CPRD covers approximately 20% of the UK’s population, the study will have a large sample size and generalisable data [16]. This will allow for several relevant subgroup analyses to be performed with sufficient statistical power.

Limitations of the study include the COVID-19 pandemic effect, which has impacted the design of the intervention. We would have liked to undertake more seminars and meet more primary care doctors, nurses, and practice managers to enhance and improve the intervention and to have done it face to face. This has not proved to be not possible due to the lockdown to contain the epidemic, which did not let me advance the intervention as we planned and wanted. Also, we had to add an extra baseline to account as 2020 was not a standard year.

Another limitation of the study is that we have no plans to contact the practices to assess if the intervention was sent. The assumption will be an increase in prescriptions is due to practices sending the intervention.

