**Fig. 1 Fig1:**
[figure not shown]
Number of asthma preventer prescription uptake by month in England [11]

This research provided the rationale for the PLEASANT study (*P*reventing and *L*essening *E*xacerbations of *A*sthma in *S*chool-age children *A*ssociated with a *N*ew *T*erm) [12]. PLEASANT was a cluster randomised trial to assess whether a letter sent from a GP practice at the start of the summer vacation reminding parents of children with asthma of the necessity of continuing to take their medication during the summer holidays. The study evaluated whether the letter increased prescriptions in August and reduced unscheduled contacts after returning to school in September [13].

The PLEASANT study included 1279 school-age children from 141 general practices (71 on intervention and 70 on control) in England and Wales. Accordingly, the results of PLEASANT showed that the letter relatively increased prescription uptake in August by 30%—an absolute increase of 4% (Fig. 2)—and reduced the unscheduled medical contacts after the return to school the period September to December (Fig. 3). Although the effects were small the intervention was cost-saving—saving £36.07 per patient over 1 year [14].

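### The claim of sufficient power for several subgroup analyses has no basis in the sample-size section and fails for some of the subgroups listed

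*Protocol article*

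**What the plan says.** The Discussion lists the size of the CPRD sample among the strengths of the study and concludes: "This will allow for several relevant subgroup analyses to be performed with sufficient statistical power".

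The Sample size section is the only place where precision is planned. It states: "The sample size is based on feasibility and the anticipated number of practices providing data to the CPRD". It then gives the inputs: "We anticipate a sample size of approximately 1389 GP practices (694 on intervention and 695 on control"; "we also anticipate 85 school-age children having asthma per practice"; "Assuming an expected rate of 30% of people collecting their prescription and an intraclass correlation of 0.03". The single output is the precision of the overall estimates, "estimated as a half-width of a 95% confidence interval—will be 1" per cent. The section states no power, target difference, subgroup size or subgroup precision.

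The Subgroup analyses section lists age (with an under-5 band), sex, ethnic group, asthma diagnosis, read receipt of the email, and the practice's IMD quintile. Each variable is to be added to the main logistic model, and an odds ratio with a 95% interval is to be reported for each group. No arm-by-subgroup interaction is named.

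The only effect size in the article is the PLEASANT result in the Background: the letter "increased prescription uptake in August by 30%—an absolute increase of 4" percentage points. The section on the intervention leaves each practice free to act or not, and gives no expected implementation rate.

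**The concern.** A statement that subgroup analyses are powered is a claim about the design, and here nothing is shown to support it. A sample that is large overall need not be large where it matters. IMD quintile is a practice-level factor, so splitting by it divides the number of clusters. The under-5 band contains only 4-year-olds, because eligibility starts at age 4.

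A reader who has been told that these analyses have sufficient power may take a null subgroup result as evidence that the effect is uniform. That would matter most for deprivation, where the design is weakest.

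**Working it through.** **Inputs from the Sample size section:** 694 and 695 practices, m = 85 children per practice, p = 0.30, ICC = 0.03. **Assumptions added here:** risk-difference scale, equal cluster sizes, no covariate adjustment, two-sided 5%, sex split 50/50, under-5s 1/13 of children (one of 13 single-year ages, 4 to 16), equal IMD quintiles.

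**1. Reproduce the plan's figure.**
- Design effect = 1 + (85 − 1) × 0.03 = 3.52.
- A = 1/(694 × 85) + 1/(695 × 85) = 3.388 × 10⁻⁵.
- SE = √(0.21 × 3.52 × A) = 0.500 points.
- Half-width = 1.96 × 0.500 = 0.98 points, against the stated 1. It agrees.
- Detectable effect at 80% power = (1.96 + 0.842) × 0.500 = 1.40 points.

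**2. Effect within a subgroup.** For a patient-level subgroup with share f, replace m by f × m.
- One sex: m = 42.5, design effect 2.245, SE = √(0.21 × 2.245 × 2A) = 0.565.
- Under 5: m = 6.54, design effect 1.166, SE = √(0.21 × 1.166 × 13A) = 1.039.
- One IMD quintile (one fifth of the practices): SE = 0.500 × √5 = 1.119.

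**3. Difference in effect between subgroups.** For a patient-level factor the shared practice effect cancels, so SE = √(0.21 × 0.97 × (1/f + 1/(1 − f)) × A).
- Sex: SE = √(0.21 × 0.97 × 4 × A) = 0.525.
- Under 5 against the rest: SE = √(0.21 × 0.97 × 14.08 × A) = 0.986.
- One quintile against another: SE = √2 × 1.119 = 1.583.

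If practice effects were independent between the sexes, the sex SE would rise to 0.799 and the detectable difference to 2.24 points. That is an upper bound.

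**4. Results.** Power is Φ(d/SE − 1.96), where d is the true effect or the true difference in effect.

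| Comparison | SE (points) | Detectable at 80% (points) | Power, d = 1 | d = 2 | d = 4 |
|---|---|---|---|---|---|
| Overall | 0.500 | 1.40 | 52% | 98% | about 100% |
| Within one sex | 0.565 | 1.58 | 42% | 94% | about 100% |
| Within under-5s | 1.039 | 2.91 | 16% | 49% | 97% |
| Within one IMD quintile | 1.119 | 3.14 | 14% | 43% | 95% |
| Difference: sex | 0.525 | 1.47 | 48% | 97% | about 100% |
| Difference: under 5 vs rest | 0.986 | 2.76 | 17% | 53% | 98% |
| Difference: one quintile vs another | 1.583 | 4.43 | 9% | 24% | 71% |

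If the arm difference is taken as PLEASANT's 4 points times the share of practices that act, d = 1, 2 and 4 correspond to 25%, 50% and 100% implementation. Neither the scaling nor the rates are in the article.

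**5. Read receipt.** The section on randomisation says that control practices receive neither the bulletin nor the email. Read status is therefore undefined in the control arm and, in the intervention arm, arises after randomisation. No sample size gives a randomised comparison within that subgroup.

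**The case against.** The Discussion says several subgroup analyses, not all of them, and does not mention interaction tests. The planned output is an odds ratio for each group, that is, a within-subgroup effect. At 4 points, within-subgroup power is about 95% or more for sex, under-5s and a single quintile. This stands, and it means the claim is not wrong for every subgroup.

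The size of the expected effect is also open. The 4 points is an August figure, while the primary outcome covers August and September with a planning rate of 30%. A 30% relative gain worth 4 points implies a base of 4/0.30 = 13.3%. The same relative gain on a 30% base would be 9 points, or 2.25 points if 25% of practices acted. That transfer is no better verified than the absolute one, but it shows how far the expected effect can move. Even then, the detectable quintile contrast of 4.43 points is about half of a full, undiluted 9-point effect. Adjustment for baseline prescriptions may also improve precision; the plan claims no gain from it and the article does not allow one to be computed.

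A reader might infer that differences between subgroups can be detected only when they are at least as large as the whole expected effect. The documents do not support that. For sex the detectable difference is 1.47 points, below a 2-point effect. What does hold for sex is narrower: a difference half the size of a 2-point effect (1 point) has 48% power.

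**Conclusion.** The unqualified power statement has no basis in the Sample size section and does not hold for some of the listed subgroups. The position differs by factor:

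- **Sex, and other evenly split patient-level factors:** adequate if the effect is about 2 points or more (94% within one sex).
- **One IMD quintile against another:** inadequate even for a difference equal to PLEASANT's 4 points (71%; 4.4 points needed for 80%).
- **Under-5s and a single quintile:** adequate at 4 points (97% and 95%), inadequate at 2 points (49% and 43%).
- **Read receipt:** no randomised comparison is possible.

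The first three rest on the assumptions listed with the calculation. The under-5 and single-quintile conclusions also depend on how far voluntary implementation dilutes the effect, which the article does not say. The stated overall precision is correct and the primary analysis is not affected.

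**What to change.** In the Discussion, delete the words about sufficient power, or limit them to evenly split patient-level factors and say for what size of effect.

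In Subgroup analyses, state that each analysis fits an arm-by-subgroup interaction term, reported with its 95% confidence interval alongside the within-group odds ratios, and label all of them exploratory. Adding the subgroup variable alone adjusts for it but does not estimate a difference in effect. Describe read receipt as a non-randomised, intervention-arm-only analysis, or remove it from the list.

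Give the detectable differences in effect (about 1.5 points for sex, 2.8 for under 5 against the rest, 4.4 for one quintile against another), noting that they are on the risk-difference scale, unadjusted, and based on assumed subgroup shares.

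The cost is a few sentences and a less favourable claim. No new data are needed, and the Trial status section says that analysis has not begun.
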